### 2.7. Intervention

#### 2.7.1. Common to Both Centres

After planning a hospital discharge, the hospital liaison nurse (HLN) will schedule the CPCP in the agenda of the PC nurse corresponding to the patient in both centres, as usual. All of them will have access to the hospital discharge report via the unified hospital and primary care digital medical record and will contact the patient’s main caregiver to assess their existing needs at home. Moreover, they will continue to perform the usual interventions included in the SACYL Portfolio of Services for CPCP (Figure S1).

Likewise, the evaluators will call the family unit upon discharge from hospital, check the inclusion criteria for this study, explain the research project, and request the signature of the informed consent form if they wish to participate. Subsequently, the initial home assessment will be planned by collecting the data described in Table 1 and the next follow-up assessments at 3, 6, and 12 months will be reported.

#### 2.7.2. Specific to the Intervention Centre

A CNCM action protocol (Figure 1) has been designed to be sequenced according to the circumstances in which the CPCPs find themselves:Pre-hospital discharge: The HLN will contact the CNCM to inform them of the imminent hospital discharge.Hospital discharge: The HLN will schedule the CPCP on the CNCM’s agenda, and the CNCM will arrange a home visit and carry out a comprehensive nursing assessment based on Marjory Gordon’s functional patterns. The main caregiver will be identified, and health education will be provided to improve home care. An infographic to identify the signs and symptoms of decompensation or exacerbation, as well as a direct-dial phone number, will also be given. The CNCM will then inform the PC team (physician, nurse, and social worker) about the patient’s situation and needs, managing necessary appointments or resources and coordinating care among professionals and levels.Post-hospital discharge proactive telephone monitoring: The CNCM will make comfort calls every week during the 1st month, every 15 days until 3 months from recruitment, and every month until 6 and 12 months (Table S2).One-month visit: The CNCM will perform a physical examination and assess adherence to treatment, the presence of decompensation/exacerbation of the process, the Barthel Index, and the satisfaction of the user or main caregiver.Occurrence of decompensation/exacerbation: If the patients and/or main caregivers report suspicious signs and/or symptoms through the direct dial telephone number, an appointment will be made with their PC physician that same day or, in the event of seriousness, urgency and/or emergency resources will be activated.Hospital readmission: The CNCM will be kept informed through the HLN and CPCP’s digital medical record. Once discharged, the process will return to the “hospital discharge” phase, and a new home visit will be scheduled to reassess the current situation.

**Figure 1 nursrep-15-00191-f001:**
[figure not shown]
Flowchart of participants’ progress. CPCP: complex and pluripathological chronic patient. CNCM: community nurse case manager. HLN: hospital liaison nurse. SACYL: Castilla y León Health System.

### 2.8. Statistical Analysis

The normality of the variables will be analysed using the Kolmogorov–Smirnov test. Continuous variables will be presented as mean ± standard deviation, or as median and interquartile range in the case of a non-normal distribution. Qualitative variables will be expressed as number and percentage. The association between qualitative variables will be analysed with the chi-square test or Fisher’s test, as appropriate. Comparisons between quantitative variables will be carried out using Student’s *t*-test or the non-parametric Mann–Whitney U test for independent measurements and paired Student’s *t*-test for related measurements. A repeated-measures analysis of variance (ANOVA) will be performed to assess the effect of the intervention between study centres. Covariates will be included in the model to control for potential confounders such as baseline functional status, comorbidities, or characteristics of the main caregiver. An alpha risk of 0.05 will be set as the limit of statistical significance for bilateral hypothesis testing. Data will be analysed with SPSS statistical software version 28.0.

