### 2.4. Sample Size Calculation

The sample size was calculated taking into account the main study variables. Specifically, it was estimated to detect a difference equal to or greater than 15 points in the Barthel Index, accepting an alpha risk of 0.05 and a beta risk of 0.2 in a bilateral contrast. Furthermore, the common standard deviation was assumed to be 34.8, as shown in the study by García-Fernández et al. [40], and a loss to follow-up rate of 20% was assumed due to the characteristics of the study subjects and the duration of follow-up. Therefore, it will be necessary to include 212 CPCPs (106 in each group) to detect statistically significant differences.

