### 2.9. Strengths and Methodological Limitations of This Study

Although this study follows all the recommendations for non-randomised interventional studies included in the TREND statement, there is a possibility of confounding factors not considered. As this study will be conducted in CPCPs, the loss rate is expected to be high, because their characteristics may prevent them from completing the follow-up due to institutionalisation or death. Given the nature of this study, subjects will not be blinded to the intervention, but the investigator in charge of analysing the data will not be aware of the centre allocation.

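### Repeated-measures ANOVA is a poor fit for a study that expects high loss from death and institutionalisation; a mixed model would keep partly observed patients

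*Protocol article*

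**What the plan says.** Section 2.8 assigns the test of the intervention to one method: "A repeated-measures analysis of variance (ANOVA) will be performed to assess the effect of the intervention between study centres". It then adds: "Covariates will be included in the model to control for potential confounders such as baseline functional status, comorbidities, or characteristics of the main caregiver". The software is given as follows: "Data will be analysed with SPSS statistical software version 28.0". The SPSS procedure is not named, and the visits that form the time factor are not listed.

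Section 2.6 and Table 1 schedule the Barthel Index, quality of life and cognition at the initial assessment and at 3, 6 and 12 months.

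On loss, section 2.4 states that "a loss to follow-up rate of 20% was assumed", and section 2.9 says that "the loss rate is expected to be high, because their characteristics may prevent them from completing the follow-up due to institutionalisation or death".

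**The concern.** Classical repeated-measures ANOVA needs a value at every level of the time factor. A patient who misses one modelled visit is left out entirely, including the visits that were made. That matters little when few visits are missed and the reasons are unrelated to health. Here the plan forecasts the opposite: substantial loss, caused by events that are plausibly more common in the functionally worst patients. The Barthel Index is a primary outcome and measures just that.

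Two things are at stake. First, the result would describe patients who survived, stayed in follow-up and were fully assessed, not the patients recruited. If the case manager changes who is lost, or if the centres lose different kinds of patient, the comparison is also biased. Second, the number analysed falls with every incomplete patient, whatever the reason, while the sample size allows for 20%.

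The complaint is not that missing-data rules are absent, since those may sit in an analysis plan that is not shown. It is that the method the article does name suits the expected data badly.

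**Working it through.** **1. Reproduce the sample size.** Inputs from section 2.4: difference 15, SD 34.8, two-sided alpha 0.05, power 0.80, loss 20%.

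n per group = 2 × [34.8 × (1.960 + 0.842) / 15]² = 84.5

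With loss: 84.5 / 0.8 = 105.6, so 106 per group and 212 in total. The stated figure reproduces.

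**2. Power when only complete patients are analysed.** With n = 106 × the complete fraction, power = Φ(15 / (34.8 × √(2/n)) − 1.96). This keeps the plan's own basis, a two-group comparison at one time point.

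| Incomplete for any reason | n per group | Power |
|---|---|---|
| 20% | 84.8 | 80.1% |
| 25% | 79.5 | 77.6% |
| 30% | 74.2 | 74.7% |
| 40% | 63.6 | 68.1% |
| 50% | 53.0 | 60.2% |

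The 20% allowance is therefore fully used at 20% incomplete. Isolated missed visits come on top of loss to follow-up. Suppose 20% are lost and 5% of the rest miss each of the 3- and 6-month visits (an assumption). The complete fraction is then 0.8 × 0.95² = 0.722, which gives 76.5 per group and 76.0% power. At 10% per visit it is 0.8 × 0.9² = 0.648, which gives 68.7 per group and 71.4% power. The documents give no rate for isolated missed visits.

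**3. Size of the selection effect.** This was checked by simulation, with 200,000 patients so that chance error is small. Taken from the plan: SD 34.8 and a 15-point effect, set equal at 3, 6 and 12 months. Assumed: mean 45, correlation 0.6 between visits, normal scores, and a logistic risk of loss before each follow-up visit that rises as the last observed score falls. The completers' estimate is adjusted for baseline. The comparison analysis uses all observed values through sequential regressions and is valid under missing at random.

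| Loss, control / intervention | Control mean at 12 months, completers (true 45.0) | Effect, completers (true 15) | Effect, all observed data |
|---|---|---|---|
| 16.1% / 13.8% | 47.4 | 14.87 | 15.03 |
| 23.0% / 17.9% | 50.8 | 14.48 | 15.01 |
| 26.2% / 22.5% | 49.0 | 14.77 | 14.96 |
| 33.0% / 26.8% | 53.3 | 14.39 | 15.12 |
| 35.0% / 30.5% | 50.3 | 14.83 | 15.11 |
| 41.0% / 33.9% | 55.3 | 14.22 | 15.02 |

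The completers' control mean is 2.4 to 10.3 points too high, so the analysed patients are clearly fitter than those recruited. The centre difference is less affected: it falls short by 0.13 to 0.78 points. Using all observed data removes the bias here because the simulated loss depends only on observed scores.

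**The case against.** **The procedure is not named.** SPSS also offers a mixed-model procedure, so it cannot be stated as fact that incomplete patients will be dropped. This stands as a qualification. The deletion follows from the classical form of the method named, and a mixed model is not what section 2.8 says.

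**The numerical harm is modest and conditional.** This also stands. The 106 per group already covers 20% incomplete, and a power shortfall needs more than that. The bias in the effect was under one point at the plan's SD. Larger figures need inputs without a source in the documents: with no true effect, SD 20 and loss of 36% against 12%, the adjusted completers' analysis is biased by −1.4 points.

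**A mixed model is no cure for death.** It assumes missing at random and implicitly carries scores beyond death. This is correct, and the fix has to deal with it.

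Two stronger readings are tempting but unsupported:

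- A reader might infer that baseline is both an outcome level and a covariate, because Barthel is measured initially and "Covariates will be included in the model to control for potential confounders such as baseline functional status". But the schedule is one of data collection, and no section makes baseline a level of the time factor. The overlap could arise directly only for Barthel, since baseline functional status is a different variable from baseline quality of life or cognition. Even if it did arise, the averaged centre effect would shrink by a quarter (11.2 against 14.9 in the simulation) with an unchanged t statistic (4.58 both ways). What remains is an ambiguity about which visits are outcomes.
- A reader might take the t and Mann–Whitney tests in section 2.8 as unadjusted effect analyses. They belong to a general list of tests; the intervention effect is assigned to the ANOVA, with covariates.

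**Conclusion.** The point holds as a mismatch between the named method and the plan's own forecast of loss. Three parts differ in certainty.

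- That a classical repeated-measures ANOVA would analyse a selected, fitter subset is well supported, given loss for the reasons section 2.9 states.
- That power drops below 80% is conditional on more than 20% of patients being incomplete. It is then about 75% at 30% incomplete and 68% at 40%.
- That the centre effect is materially biased is not shown. The bias was under one Barthel point in the scenarios tested, which rest on an assumed correlation and an assumed loss mechanism. Stronger differences between centres in who is lost could make it larger.

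This is worth fixing before analysis because a better method is available in the same software. It is not a flaw that would by itself overturn the result.

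**What to change.** In section 2.8, replace the repeated-measures ANOVA with a linear mixed model for repeated measures:

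- **Outcomes:** the 3-, 6- and 12-month values. This also settles which visits are outcome levels.
- **Fixed effects:** centre, visit, centre-by-visit, the baseline value of the outcome being analysed, and the confounders already planned.
- **Patients:** all with at least one follow-up value.

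State that the model assumes missing at random. Because it extrapolates implicitly after death, report deaths and institutionalisation by centre, and add a sensitivity analysis that ranks death as the worst outcome.

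The cost is changed wording and slightly more analysis work in the software already chosen. The model needs no extra visits or measurements. The trade-off is reliance on the missing-at-random assumption, which the reporting of deaths and the sensitivity analysis help to examine but cannot verify.

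### The repeated-measures ANOVA in 2.8 drops every patient with a missed assessment, so in a trial that expects high loss it discards collected primary data and compares selected completers

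*Protocol article*

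**What the plan says.** Section 2.8 of the protocol article names one method for the intervention effect: "A repeated-measures analysis of variance (ANOVA) will be performed to assess the effect of the intervention between study centres". It adds: "Covariates will be included in the model to control for potential confounders such as baseline functional status, comorbidities, or characteristics of the main caregiver". The software is fixed as well: "Data will be analysed with SPSS statistical software version 28.0".

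Table 1 schedules all three primary outcomes (Barthel Index, COOP-WONCA, MoCA) at the initial assessment and at 3, 6 and 12 months.

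On attrition, section 2.9 says that "the loss rate is expected to be high, because their characteristics may prevent them from completing the follow-up due to institutionalisation or death". Section 2.4 allows for it once, in the sample size: "a loss to follow-up rate of 20% was assumed due to the characteristics of the study subjects and the duration of follow-up".

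**The concern.** A classical repeated-measures ANOVA needs a complete row for each patient. In the SPSS general linear model procedure, a patient measured at baseline, 3 and 6 months who then dies or moves to an institution leaves the analysis altogether. So does a patient who misses only the 3-month visit, or who lacks one covariate.

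That fits badly with what the article itself expects. The two named causes of loss are plausibly linked to worsening function, so the patients removed are unlikely to resemble those kept. Their earlier scores, which carry information about why they left, are removed with them. What remains is a comparison of patients who survived, stayed at home and kept every visit. In a non-randomised comparison of two centres this adds a second source of selection to the confounding that section 2.9 already acknowledges. It applies to all three primary outcomes.

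**Working it through.** **1. The plan's sample size reproduces.** Inputs from 2.4: difference 15 Barthel points, SD 34.8, two-sided alpha 0.05, power 80%, 20% loss.

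- n per arm = 2 × (1.960 + 0.842)² × 34.8² / 15² = 84.5
- Inflated for loss: 84.5 / 0.8 = 105.6, so 106 per arm and 212 in total, as stated.
- Evaluable per arm after 20% loss: 106 × 0.8 = 84.8, about 85. The article does not print this figure; it follows from its inputs.

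**2. Is the planned number met under deletion of incomplete patients?** Complete patients per arm = 106 × (1 − share with any missed visit).

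| Share with any missed visit | Complete per arm |
|---|---|
| 20% (the plan's figure) | 84.8 |
| 25% (assumed) | 79.5 |
| 30% (assumed) | 74.2 |
| 40% (assumed) | 63.6 |

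If the 20% covers everyone who misses any visit, the number is met. If instead 20% are lost by month 12 and each remaining patient also misses the 3- or 6-month visit with probability m, the count is 106 × 0.80 × (1 − m)². For assumed m of 2%, 5% and 10% this gives 81.4, 76.5 and 68.7. The article gives no value for m.

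**3. How much collected data is discarded?** Assume 20% are lost by month 12 at a constant rate, with no intermittent misses. Patients present at month t = 106 × 0.8^(t/12).

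- 3 months: 100.2; 6 months: 94.8; 12 months: 84.8
- Follow-up records collected per arm, for each outcome: 100.2 + 94.8 + 84.8 = 279.9 (from unrounded counts)
- Records used by the ANOVA: 3 × 84.8 = 254.4
- Discarded: 279.9 − 254.4 = 25.5, and 25.5 / 279.9 = 9.1%
- Baseline scores also unused: 106 − 84.8 = 21.2

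With 30% or 40% lost (assumed), the same arithmetic discards 37.2 of 259.8 (14%) or 48.2 of 239.0 (20%).

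**4. How much can be kept?** Under the 20% assumption, 100.2 − 84.8 = 15.4 patients per arm have at least one follow-up score but not all three. A mixed model keeps them. The other 106 − 100.2 = 5.8 have no follow-up score and are not used by a model with baseline as a covariate.

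**The case against.** **A reader might infer that the trial misses its planned number or its 80% power.** The article does not support that. Its own 20% allowance leaves 84.8 per arm. A shortfall needs either loss above 20% or intermittent misses in addition to it, and no such rate is given. Nothing in 2.4 says that the 20% excludes patients who miss a middle visit.

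Nor can lower power figures be read off the smaller counts. The unadjusted two-group formula at one time point gives 80.1% at 84.8 per arm and 77.6%, 74.7% and 68.1% at 79.5, 74.2 and 63.6. The stated analysis, however, adjusts for baseline function and uses repeated measures. If baseline and outcome correlate at 0.60 (assumed), the residual SD is 34.8 × √(1 − 0.60²) = 27.84. The same formula, Φ(15 / (27.84 × √(2/n)) − 1.96), then gives 92%, 91% and 86% at those three counts. The ANOVA's power depends on within-patient correlations that the article does not give.

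**A reader might also infer a bias of known size, driven by unequal contact.** Only the intervention centre has case-manager calls: "The CNCM will make comfort calls every week during the 1st month, every 15 days until 3 months from recruitment", then monthly. But section 2.7.1 has primary care nurses contact caregivers in both centres, and independent evaluators run the assessments in both. Different completion by centre is possible, not shown. The size of any bias depends on a dropout mechanism that would have to be assumed.

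**The full plan may impute.** It is not shown, and imputation would keep these patients. So the point rests on the method that 2.8 names, not on the lack of a missing-data section.

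**A mixed model does not solve death.** This stands. Death is one of the two named causes of loss, and the model gives no meaning to a Barthel score after it.

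**Conclusion.** The point holds in a limited form: the method named in 2.8 fits badly with the loss expected in 2.9. It discards primary-outcome scores already collected, even when the 20% allowance is exactly right, and it compares selected completers. About 9% of follow-up records per arm are lost to the analysis under 20% loss at a constant rate, and more if loss is higher or visits are missed intermittently. This rests on the usual deletion of incomplete rows in SPSS, with no imputation added elsewhere.

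The sample size is correct as calculated. The implied 85 per arm is missed only if more than 20% of patients lack at least one visit. No power figure or bias size should be attached to this point. It is a cheap improvement to the analysis, not a fault in the design.

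**What to change.** In 2.8, replace the repeated-measures ANOVA for the Barthel Index, COOP-WONCA, MoCA and the other continuous outcomes with a linear mixed model for repeated measures (SPSS MIXED, REML, unstructured covariance across 3, 6 and 12 months). Include every patient with at least one follow-up value. Fixed effects: centre, visit, centre-by-visit, the outcome's own baseline and the confounders already named in 2.8. State that deaths and institutionalisation will be reported by centre beside the model results.

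The cost is one paragraph of wording; the data and the software stay the same. There are three limits to state openly. The model relies on missing at random. It estimates values for patients who died as if they were still observed, which is why the counts by centre are needed. And a patient with a missing baseline covariate is still dropped, so those fields should be completed at the initial assessment.

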##### Quality of Life

This will be assessed using the Spanish version of the COOP-WONCA test, which shows acceptable internal consistency (Cronbach’s alpha = 0.73). This instrument relates the patient’s quality of life to their health during the last four weeks by asking about their physical fitness, feelings, daily activities, social activities, state of health, changes in their state of health, and pain by means of a drawing representing a degree of functioning with a 5-level Likert scale. Higher scores express worse levels of functioning/well-being [43].

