##### Cognitive Performance

This will be explored through the Montreal Cognitive Assessment (MoCA), which consists of 30 items and lasts approximately 10–12 min. It helps to identify mild impairments in cognitive skills (orientation, short-term memory/delayed recall, executive function/visuospatial ability, language, abstraction, identification, and attention). The total score is 30 points; a score of 26 or higher is considered normal. Cronbach’s alpha for the Spanish version was 0.77 [44].

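### Three outcomes are declared primary under one unadjusted 0.05 limit but only Barthel is sized, so the stated 5% alpha and 80% power do not describe the primary set

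*Protocol article*

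**What the plan says.** All references are to the protocol article.

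- **Primary outcomes (2.5.2).** Three instruments stand under this heading before the secondary outcomes begin in 2.5.3. The first is the Barthel Index for activities of daily living. The second is quality of life: "This will be assessed using the Spanish version of the COOP-WONCA test". The third is cognition: "This will be explored through the Montreal Cognitive Assessment (MoCA"). Table 1 schedules all three at baseline and at 3, 6 and 12 months.
- **Significance limit (2.8).** "An alpha risk of 0.05 will be set as the limit of statistical significance for bilateral hypothesis testing". The section gives no order among the three outcomes, no division of alpha, and no statement of whether one positive outcome or all three are needed for a primary claim.
- **Test of the intervention (2.8).** The effect between centres is assessed by repeated-measures ANOVA with covariates. Student's t and Mann–Whitney tests are also listed, without saying for which visits or outcomes.
- **Sample size (2.4).** The opening sentence says the main variables, in the plural, were taken into account. The calculation then names one: "it was estimated to detect a difference equal to or greater than 15 points in the Barthel Index". It gives that single outcome a two-sided alpha of 0.05 and 80% power. No difference or standard deviation is given for COOP-WONCA or MoCA.

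**The concern.** A 5% limit controls the risk of a false claim for one test. When three outcomes each carry primary status and each is tested at 0.05, the risk that at least one is falsely positive exceeds 5%, unless a positive result on all three is required. The sizing does not match either rule: it gives Barthel the whole 0.05 and says nothing about the other two.

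This affects what can be claimed. The Discussion links the results to recognising the case manager as a professional category, and the Conclusions to decisions on organising care. A claim resting on whichever of the three primaries reached p < 0.05 would not carry the stated error rate. A claim requiring all three would not have the stated power.

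**Working it through.** **1. Reproduce the plan's own figure.** Inputs, all from 2.4: difference 15 points; "the common standard deviation was assumed to be 34.8"; two-sided alpha 0.05 (z = 1.960); power 0.80 (z = 0.842); "a loss to follow-up rate of 20% was assumed"; equal groups.

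n per arm = 2 × [SD × (z_alpha/2 + z_power) / difference]² = 2 × [34.8 × 2.802 / 15]² = 84.49.

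Allowing for loss: 84.49 / 0.80 = 105.6, rounded up to 106 per arm, so 2 × 106 = 212. This matches the stated total. (Rounding to 85 before dividing gives 107 per arm, or 214, an immaterial difference.) The figure is therefore right for Barthel alone at the full 0.05. It contains no allowance for sharing alpha with two other outcomes.

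**2. Any one of three counts as success, one ANOVA test per outcome.** This assumes no effect on any outcome and one named ANOVA effect per outcome. If the tests are independent:

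1 − (1 − 0.05)³ = 1 − 0.857375 = 0.1426, or 14.3%.

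The article gives no correlations, so these are assumed. Simulation from a multivariate normal distribution with equal correlation between the three test statistics (1,000,000 draws, two-sided 0.05 each) gives:

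| Assumed correlation | Chance of at least one false positive |
|---|---|
| 0 | 14.3% |
| 0.3 | 13.6% |
| 0.5 | 12.6% |
| 0.7 | 10.9% |
| 0.8 | about 10% |

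The range is about 10–14%, two to three times the nominal level.

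**3. Any one of three, with each visit also tested separately.** The text permits this but does not specify it. Nine tests (three outcomes × three visits) need two assumed correlations. Simulation with 400,000 draws gives:

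| Between outcomes | Between visits | Chance of at least one false positive |
|---|---|---|
| 0.3 | 0.6 | 30.1% |
| 0.5 | 0.7 | 25.9% |
| 0.5 | 0.8 | 23.5% |
| 0.5 | 0.9 | 20.2% |

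That is about 20–30% for these values. The extremes examined were 37.0% (nine independent tests) and 15.9% (0.8 and 0.9).

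**4. All three required.** The chance of falsely claiming success on all three cannot exceed 5%, so alpha holds. Power for the joint claim cannot exceed that of the weakest outcome, and for two of the three it was not calculated. For illustration only, three independent outcomes with 80% power each would give 0.8³ = 51.2% joint power; perfect correlation would give 80%. The actual figure cannot be derived from the article.

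**The case against.** **The SAP may hold the rule.** A testing order, multiplicity procedure or primary time point is often placed in the SAP or full protocol, and neither is shown. That is fair, and their absence alone is not the point. The point rests on what the article prints: three primaries, one flat 0.05 limit, and a sample size described in the plural but computed for one outcome. A rule elsewhere would have to override the flat limit. It would also leave the sizing in 2.4 without its basis unless Barthel kept the full 0.05.

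**No any-of-three rule is stated.** This is correct. The Abstract and Expected Results anticipate improvement across the outcomes, which could be read as needing all three. The 10–14% is therefore conditional. The alternative rule removes the alpha problem and puts a power problem in its place.

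**Stronger readings that the documents do not support.** A reader might infer that every primary outcome is tested at every visit, so that an error rate near 30% is built into the plan. Section 2.8 assesses the intervention by repeated-measures ANOVA, which can give one test per outcome; the t-test and Mann–Whitney sentence is generic. A reader might also infer that the seven COOP-WONCA domains are seven separate tests. Section 2.5.2 describes the domains but does not say they are analysed one by one. Nor does it follow that Barthel loses power through a Bonferroni split: the plan proposes no split, and the fix below needs none.

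**This is a pilot.** The aim is to pilot the role in a non-randomised comparison with one centre per arm, and the article acknowledges limits of the design. Centre differences are confounded with treatment, so naming one primary outcome would not by itself secure a true 5% error rate. This stands, and it lowers the severity. It does not make the stated alpha and power fit the declared primary set.

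**Conclusion.** The point holds in a limited form. The article's 5% and 80% describe one outcome, Barthel, while three are declared primary. Under an any-of-three rule with one ANOVA test per outcome, the chance of at least one false positive primary finding is about 10–14%, over assumed correlations from 0.8 down to 0. It would reach about 20–30% only if visits were also tested separately, which is an assumption about the analysis as well as about the correlations. Under an all-three rule alpha holds, but the power is unknown. The total of 212 is not in error for Barthel. Severity: should be fixed.

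**What to change.** - In 2.5.2, make the Barthel Index, the only outcome sized, the single primary endpoint at two-sided 0.05.
- In 2.8, pre-state one contrast for it: for example the 12-month comparison, as the final visit, or one named ANOVA effect. The article names no primary time point, so this choice belongs to the sponsor.
- Move COOP-WONCA (as one pre-stated summary score) and MoCA to key secondary outcomes, tested in fixed order or with Holm.
- Treat results at other visits as supportive and report them with confidence intervals.
- In 2.4, state that 212 is sized for Barthel only.

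The cost is protocol wording and a registry update. The downside is that COOP-WONCA and MoCA lose co-primary status. N stays at 212.
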